## Abstract

**Background:**

Dentofacial malformation is a common condition that affects a significant portion of the population, resulting in functional and aesthetic defects. Orthognathic surgeries, such as LeFort I osteotomy, are performed to correct these abnormalities. However, the impact of these surgeries on nasal profile changes remains unclear. Additionally, the role of anterior nasal spine (ANS) reduction in maxillary advancement surgeries of 3–5 mm range is yet to be determined. This study aims to investigate the effect of ANS reduction on soft tissue profile changes following LeFort I osteotomy with a maxillary advancement range of 3–5 mm in class III skeletal patients. The hypothesis is that the changes in nasolabial angle and upper lip length will not significantly differ between patients who undergo LeFort I osteotomy with and without ANS reduction.

**Method and design:**

This study is designed as a randomized controlled trial. A total of 26 class III skeletal patients with maxillofacial abnormalities will be recruited from the maxillofacial clinic of Bu-Ali and Farahikhtegan Hospitals in Tehran, Iran. Patients meeting the inclusion criteria will be randomly assigned to two groups: one group will undergo LeFort I osteotomy with ANS reduction, and the other group will undergo LeFort I osteotomy without ANS reduction. The soft tissue profile changes, specifically the nasolabial angle and upper lip length, will be evaluated and compared between the two groups.

**Discussion:**

Achieving facial harmony through orthognathic surgery requires careful planning and consideration of the impact on surrounding soft tissue. The primary objective is to predict and plan for the effects on the nasolabial region. LeFort I osteotomy is a common procedure used to correct dentofacial deformities, particularly in class III patients. Maxillary advancement during this surgery can lead to changes in nasal tip position, width, and rotation, potentially due to repositioning of the anterior nasal spine and soft tissue dissection. In this study, soft tissue changes will be assessed in non-growing class III patients using cephalometric radiographs. The impact of reducing the anterior nasal spine (ANS) on nasal profile changes will be investigated for maxillary advancements of 3–5 mm. Objective measurements and patient-reported outcomes will be evaluated to gain insights into the aesthetic outcomes of orthognathic surgery. The findings will provide valuable guidance for treatment decisions and alternative options based on expected nasal profile changes.

**Trial registration:**

This project was registered at The Iranian Registry of Clinical Trials (Identifier No. IRCT20210928052625N1, Website: https://www.irct.ir/trial/59171) and Open Science Framework (OSF) (Registration https://doi.org/10.17605/OSF.IO/X3HD4). 2021-06-09.

**Supplementary Information:**

The online version contains supplementary material available at 10.1186/s13063-024-08162-1.

## Introduction

Dentofacial malformation is the deviation of facial skeletal development from its correct and normal process, which manifests itself with changes in appearance, malocclusion, and functional problems [1]. This anomaly affects approximately 20% of the population and includes a different spectrum of functional and aesthetic defects. Dentofacial deformity can be limited to the maxilla or mandible or spread to more structures. It can also be unilateral or bilateral and in a different amount in terms of longitudinal, transverse, or vertical dimensions [2]. Orthognathic surgeries are used to treat these abnormalities. The time to perform these surgeries is after the end of growth and will be performed if orthodontic treatment alone is not enough to solve these abnormalities. Orthognathic surgery along with orthodontic treatment will result in more stable outcomes in terms of improving facial appearance and function [3]. The success of the treatment depends on the diagnosis and the appropriate treatment plan and the skill of the surgeon, and the change in the hard tissues changes the shape of the soft tissue [4]. The technique and knowledge of orthognathic surgeries have made great progress in recent years, but our understanding and awareness in terms of predicting soft tissue changes remains limited [5, 6]. The most changes of the soft tissue after LeFort 1 osteotomy surgery are related to nose type, nasolabial angle, alar base width and upper lip position, and height [7]. Some of these soft tissue changes lead to better cosmetic results and are therefore desirable, and therefore we allow them to occur after surgery. For example, a patient who has a small interalar space before LeFort 1 osteotomy surgery will benefit from maxilla advancement. Because this surgery will increase this distance, and for this patient it is considered a favorable result in terms of aesthetics.

On the other hand, by predicting changes that may have an adverse effect on beauty, these effects can be reduced by taking auxiliary measures during surgery, or by informing the patient before surgery, with the help of secondary surgeries to fix these problems [8]. The nose is an important part of facial beauty. LeFort 1 osteotomy and maxillary movements affect the position and shape of the nose. In some studies, widening of the base of the nose following LeFort 1 osteotomy has been reported [9]. In general, changes in the nose have remained contradictory and unclear in studies. In any case, it is necessary for the surgeon and the patient to be aware of possible soft tissue changes following surgery and to know that they may need secondary corrective surgeries to achieve the desired aesthetic results after surgery [10]. The existing literature review indicates that there is a significant debate surrounding the alterations in nasolabial soft tissue following maxillary advancement surgery so, there is not a consensus idea on the alterations of LeFort I Maxillary Surgery in nasolabial soft tissue. Based on the Surgeons’ experience in this Study, we have ANS reduction for cases above 5 mm of maxillary advancement, and below 3 mm does not require ANS reduction [11]. Still, in cases where we have maxillary advancement between 3 and 5 mm, some surgeons tend to reduce ANS and some do not, so the purpose of our study is to find out that which method is better in the range of 3–5 mm.

### Objective and hypothesis

The major goal of this double arm parallel randomized clinical trial is to see how reducing ANS affects the soft tissue profile after maxillary advancement surgery with an advancement range of 3–5 mm. The null hypothesis is that the changes of nasolabial angle and upper lip length in skeletal class III patients of the study after LeFort 1 osteotomy (maxillary advancement) with and without ANS reduction are not significantly different.

## Methods

### Overview

This research is planned as a randomized controlled trial. The goal is to enroll 26 class III skeletal patients from the patients who refer to the maxillofacial clinic of Bu-Ali and Farahikhtegan Hospitals in Tehran, Iran, who suffer from maxillofacial abnormalities. We will have 2 groups: (1) control group (without ANS reduction) and (2) intervention group (with ANS reduction). This project was registered at The Iranian Registry of Clinical Trials (Identifier No. IRCT20210928052625N1, Website: https://www.irct.ir/trial/59171) and Open Science Framework (OSF) (Registration 10.17605/OSF.IO/X3HD4). Recruiting and treatment methodology of this study is confirmed by the Research Ethics Committee of the Islamic Azad University Dental Branch, Tehran, Iran (IR.IAU.DENTAL.REC.1400.035). Each participant’s overall health will be assessed by researchers before creating a treatment plan (Fig. 1 and Table 1).

**Fig. 1 Fig1:**
[figure not shown]
Flow chart of the treatment process. “*” symbol indicates the following: M, month

**Table 1 Tab1:** SPIRIT figure

	**Study period**			
	**Enrolment**	**Allocation**		
	**Prior to allocation**	**Month** **0**	**Month** **3**	**Month** **4**
Case selection Allocation Hygiene education	*	*		
Orthognathic surgery and pre-operative lateral cephalometry		*	*	*
3 month recovering time				*
Post-operative lateral cephalometry			*	*

Inclusion criteria:The amount of maxillary advancement should be 3–5 mm.Participants must be between 20 and 50 years to enter the study.

Exclusion criteria:Presence of Jaw surgery in the medical historyPresence of rhinoplasty or any other nose surgeries in medical historyNeed of maxillary advancement below 3 mmNeed of maxillary advancement more than 5 mmAny systemic or local diseases that may interfere with bone repair (including hypothyroidism, osteoarthritis, hyperparathyroidism, diabetes, and osteoporosis)Using bisphosphonatesPregnancySmoking or drug addictionPatient undergoing radiotherapyPresence of syndromes or cleft palates [3, 12]

Patients who with any of these requirements will be excluded from the research.

### Recruitment

Patients with skeletal class III pattern, with maxillofacial disorders, are eligible for a maxillary advancement surgery. Between 2023 and 2024, patients are sent to the Oral and Maxillofacial Surgery Department, Bu-Ali and Farhikhtegan Hospitals, Tehran, Iran. Patients who meet the criteria will receive a written consent form that clearly explains the details of the study in simple language. The researchers will also verbally explain the background of the research, how it will be conducted, what participation involves, any potential risks, and the rules regarding confidentiality. Participants have the right to ask questions and receive all the necessary information about the study. Prior to enrolling in the research, each patient must sign a consent form to confirm their understanding of the study’s objectives. They will then proceed to join the research after expressing their willingness to participate.

## Allocation and randomization

### Randomization

Every participant will receive a unique numerical code, which will be enclosed within a securely sealed envelope. The envelopes will remain unopened until the procedure is conducted by external investigators. As a result, the participants will be divided into two groups: group 1 (with ANS reduction) and group 2 (without ANS reduction). An independent investigator will utilize a web-based randomization service available at www.randomization.com to generate a randomized sequence. The envelopes are opened during the surgery by surgical assistant. Until that moment, the result of the allocation process in each sample is not known.

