### Intervention

For these patients, a standard lateral cephalometry (the ORTHOPHOS brand device, which has a voltage of 200 to 240 volts and takes images with an output of 230 volts) is prepared before the operation, and the points and angles of the study will be analyzed using a gauge and a calibrated protractor [5, 10, 13, 14]. On the day of the operation, two sets of surgery are prepared according to the two types of study interventions, and at that time, the corresponding envelope is opened according to the order of referral and the patient’s assigned code, and the type of intervention is determined. We have 2 groups: the control group will not have any ANS reduction, and the test group will have ANS reduction. For patients undergoing surgery, after the patient is anesthetized by the anesthesia service, the routine preparation and the necessary injections will be performed in the surgical areas. Then, we will start the incision with the surgical blade no. 15 in the depth of the buccal vestibule of the upper jaw from the alignment of upper right first molar (16) to upper left first molar (26), the flap is pushed aside, and the periosteum will be separated from the bone in order to have the access to the bone for LeFort I incision. Then, the osteotomy lines are drawn and cut with a saw, and the maxilla will be separated from the base of the nose after the down fracture; then, the maxilla is placed in a new and appropriate position (advancement 3–5 mm) and by two “L” plates with 4 holes, and two straight plates with 4 holes will be fixed. If there is a need for ANS reduction, the ANS is completely removed by a large-sized round carbide bur. The surgical process continues, and after the surgery, we will follow-up the patient for 3 months, and after 3 months, we will request a post-op radiography to collect final data [15].

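### The article gives two times for opening the allocation envelope, and neither is tied to fixation of the maxilla, so the unblinded surgeon may know the arm while setting the advancement

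*Protocol article*

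**What the plan says.** All references are to the protocol article.

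- **Randomization, on timing and opener.** "The envelopes are opened during the surgery by surgical assistant". The section adds that no patient's allocation is known until then. It also says "The envelopes will remain unopened until the procedure is conducted by external investigators", which brings in a second role that does not match the surgical assistant.
- **Intervention, on timing.** This section sets the opening on the operation day: "two sets of surgery are prepared according to the two types of study interventions, and at that time, the corresponding envelope is opened". No opener is named. The text goes on to say that "after the patient is anesthetized by the anesthesia service, the routine preparation and the necessary injections will be performed in the surgical areas", and then describes incision, osteotomy, down fracture, placement of the maxilla at 3–5 mm, plate fixation and, last, the ANS step.
- **Intervention, on the ANS step.** "If there is a need for ANS reduction, the ANS is completely removed". An earlier sentence in the same section already ties reduction to the test group and no reduction to the control group.
- **Blinding; Training and calibration.** The operator cannot be blinded, and one specialist performs all the surgery. Patients, the data assessor and the statisticians are to be unaware of the allocation.
- **Arm numbering.** Overview: "1) control group (without ANS reduction) and (2) intervention group (with ANS reduction". Randomization: "group 1 (with ANS reduction) and group 2 (without ANS reduction".

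**The concern.** The two sections do not describe the same moment. The Intervention section, taken in its written order, reveals the arm before surgery starts. The Randomization section reveals it at some unspecified point during surgery.

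The moment that matters for bias is fixation of the maxilla. The arms are meant to differ only in the ANS step. If the surgeon knows the arm before the maxilla is fixed, he could, without intending to, place it differently in the two arms. Randomization cannot remove a difference that arises after the arm is revealed. The article itself treats the amount of advancement as relevant to the ANS question: the Introduction describes the surgeons' practice above 5 mm and below 3 mm as settled, and only the range between as open. A difference in achieved advancement between arms would therefore be mixed with the effect under study.

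The opposite arm order in the Overview and Randomization sections is a smaller matter. The statisticians are blinded to assignment, so if they work from numeric codes they would be badly placed to notice a mix-up.

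**Working it through.** **Step 1. Order of events in the two sections.**

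| Event | Randomization | Intervention |
|---|---|---|
| Who opens | surgical assistant (external investigators also mentioned) | not named |
| When opened | during surgery | operation day, when the two sets are prepared |
| Before or after anaesthesia | after, by implication | before, in the order of the text |
| Before or after fixation of the maxilla | not stated | before, in the order of the text |
| ANS step | not described | after fixation |

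The conflict is in the timing relative to anaesthesia. The gap common to both is that neither makes opening wait for fixation. Choosing the Randomization wording alone would therefore settle the contradiction without closing the gap.

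**Step 2. What the surgeon could influence.** Inclusion requires an advancement of 3–5 mm, and a need below 3 mm or above 5 mm is an exclusion. The needed amount is thus judged before entry and before allocation under either reading. What is left is the final placement in theatre, which the Intervention section describes as an appropriate position within 3–5 mm. The article does not say how far that placement may depart from the plan.

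**Step 3. Illustration of size.** The article gives no figure for change in nasolabial angle or lip length per millimetre, so the shift has to be assumed. Inputs: n = 13 per arm (Sample size), two-sided α = 0.05 (Statistical analysis), and no true effect of ANS reduction. For simplicity the check uses a two-sample t-test on the change. A spurious difference of d SD gives

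- degrees of freedom 2 × 13 − 2 = 24, critical value 2.064;
- noncentrality d × √(13/2) = 2.550 × d;
- rejection probability P(|T| > 2.064), with T noncentral t.

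| Assumed shift d | Noncentrality | Rejection probability |
|---|---|---|
| 0 | 0 | 5.0% |
| 0.1 SD | 0.255 | 5.7% |
| 0.2 SD | 0.510 | 7.8% |
| 0.3 SD | 0.765 | 11.4% |

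These show how sensitive a trial of this size is to a small systematic difference. They do not estimate the bias in this trial.

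**Step 4. Arm numbering.** The Overview lists control first and ANS reduction second; the Randomization section numbers them the other way round. The Overview figures are list numbers in front of named arms, and only the Randomization section defines a group 1 and a group 2. The Intervention section uses control and test.

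The planned sample size does not enter the argument except as n = 13, and none of these points changes it.

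**The case against.** The strongest reply is that the two timings can be reconciled. The phrase in the Intervention section may refer loosely to the operation day, and preparing both sets makes most sense if the arm is still unknown at set-up. The envelope sentence also stands ahead of a general description of the arms, so its place in the paragraph is weak evidence of operative order. This stands in part: the conflict is less than absolute. A reader following the text literally would still open the envelope before anaesthesia, and no reading places the opening after fixation.

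Four stronger readings are tempting and are not supported:

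- **That concealment is broken.** Both versions open the envelope on the operation day, after consent and eligibility.
- **That the surgeon has a free 2 mm choice, up to 67% more advancement ((5 − 3)/3).** The 3–5 mm range is an eligibility range across patients, and each patient's need is judged beforehand. It does not measure discretion within a patient. Nor does the article say that advancement is the main cause of the soft-tissue change.
- **That the conditional wording of the ANS step leaves reduction to the surgeon's judgement.** The same section states the arm rule explicitly just before. The wording is loose, and the allocation governs.
- **That the reversed numbering will flip the result.** That would need an error in the unblinding key, which nothing in the article shows.

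It can also be said that opening after fixation goes beyond reconciling the text, since neither section promises it. That is true. It is an improvement recommended because it is nearly free.

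**Conclusion.** The point holds as a matter of reconciliation plus a cheap safeguard. The article states two opening times and is unclear about the opener, and it does not prevent an unblinded surgeon from knowing the arm while finalising the position of the maxilla. The consequence is possible performance bias whose size cannot be derived from the article; it may be small, because the needed advancement is set before allocation. The range of 5.7% to 11.4% rests on assumed shifts of 0.1 to 0.3 SD and on a simple t-test, and should be quoted only with that label. The opposite arm numbering is a clerical inconsistency that carries a risk of a code mix-up; no such error is shown.

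**What to change.** 1. State one rule, in the same words, in the Randomization and Intervention sections. For example: *The surgical assistant opens the envelope only after the maxilla has been fixed and the achieved advancement in mm has been recorded; the ANS step then follows the allocation.* Remove or explain the reference to external investigators.
2. In the Intervention section, make the ANS step conditional on allocation: *if allocated to ANS reduction*.
3. Use one arm numbering in the Overview and Randomization sections.

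The first change leaves the operative sequence as the Intervention section describes it: the ANS step already follows fixation, and both sets are already prepared. The cost is one line in the operating log and opening the envelope somewhat later. The recorded advancement also allows the two arms to be compared on it. The other two changes are wording only. For operations already done, any existing records should be checked for when the envelope was opened and which group code was used.

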### Blinding

The operator cannot be blinded, but the treatment assignment will be kept concealed from the data assessor. Additionally, all patients will be unaware of their group allocation. Operators will not have access to statistical assessment tools to maintain blinding. Similarly, statisticians will remain unaware of the treatments and group assignments.

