The second lateral cephalometry will be requested from the same radiology center in the same position as the previous one. The desired data for the research work will be measured by the same person with the same equipment; it should be noted that all the cephalometric measurements (the baseline and follow-up radiographs) will be measured twice, and the average is recorded as the desired number of that variable; then, the obtained results will be subjected to statistical analysis (Fig. 1). The patients will be excluded from the trial if they get pregnant, leave their orthodontic treatment half-finished, or leave the study at their own will.

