### Outcomes

An oral and maxillofacial radiologist will assess the nasolabial angle and upper lip length using a lateral cephalometry before the surgery. Three months following surgery, a second lateral cephalometry will be performed. With the same basic evaluation methods, nasolabial angle and upper lip length will be assessed.

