### Statistical analysis

To assess the consistency of descriptive data, Cohen’s *k* statistic will be employed. Descriptive statistics, such as frequency counts (both absolute and relative) and metric data (such as arithmetic mean, standard deviation, and median), serve as examples of the types of statistics used. The consistency between the two examiners for continuous data, such as clinical parameters, will be assessed using the intraclass correlation coefficient. Enumerated data will be presented as percentages, while measured data will be reported as mean standard deviation or median (quartile spacing). We will assess the effects of differences in measurement time between the two study groups at baseline and follow-up by conducting an analysis of variance (ANOVA), considering the type of intervention as a factor. All statistical analyses will be conducted using SPSS 25.0. The significance threshold is set at 0.05.

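### Assessor blinding is claimed but not secured: removal of the ANS in one arm is likely to show on the follow-up films from which both outcomes are read

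*Protocol article*

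**What the plan says.** All references are to the protocol article.

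- **Blinding:** the operator is not blinded, but "the treatment assignment will be kept concealed from the data assessor". Patients and statisticians are also said to be unaware of allocation.
- **Intervention, the arms:** "the control group will not have any ANS reduction, and the test group will have ANS reduction". Where reduction is done, "the ANS is completely removed by a large-sized round carbide bur".
- **Intervention, the measurement:** "the points and angles of the study will be analyzed using a gauge and a calibrated protractor". Baseline and follow-up data "will be measured by the same person with the same equipment", each measurement being made twice and averaged.
- **Outcomes:** "An oral and maxillofacial radiologist will assess the nasolabial angle and upper lip length using a lateral cephalometry before the surgery". For follow-up, "Three months following surgery, a second lateral cephalometry will be performed", and the same two quantities are assessed in the same way. Neither is labelled primary, but they are the only outcomes in this section and in the null hypothesis.
- **Training and calibration:** an independent investigator measures before and after surgery, and one surgeon performs all operations.
- **Statistical analysis:** "The consistency between the two examiners for continuous data, such as clinical parameters, will be assessed using the intraclass correlation coefficient".

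No section describes covering the ANS region, working from a soft-tissue outline alone, or any other step that would hide the spine from the reader.

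**The concern.** The allocation code can be kept from the reader, but the film itself carries the information. The experimental difference is a midline bony structure, present or absent, in the region shown on the image from which the outcomes are taken. The reader has also measured the same patient's baseline film, taken before any ANS removal.

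Placing soft-tissue landmarks and reading an angle by hand involve judgement. A reader who can see the arm may, without intending to, place landmarks differently in the two arms. With a single reader and 13 patients per arm, such a shift cannot be told apart from a treatment effect, and no later analysis can remove it. Averaging two readings by the same person reduces random error but leaves a systematic shift untouched. Because the surgeon is necessarily unblinded, masking of the reader is the main protection that these measurements have.

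**Working it through.** **1. What the described procedure conceals.**

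| Safeguard in the article | What it hides | Does it hide the ANS on the follow-up film? |
|---|---|---|
| Sealed envelopes, opened in theatre | The allocation code before surgery | No |
| Independent investigator measures | The reader's knowledge from the operation | No |
| Surgeon is a separate person | Same | No |
| Each measurement made twice and averaged | Nothing; reduces random error | No |
| Statisticians unaware of groups | Group labels at analysis | No |

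The fixation plates are used in both arms. They mark a film as post-operative but do not mark the arm. The ANS is the feature that differs by design.

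**2. The plan's own figure, to set the scale.** The Sample size section gives 13 per group, using a between-group effect size of 0.6. Its type is not stated and the wording on α and β is unclear. I read the effect size as Cohen's f, so d = 2 × 0.6 = 1.2, with α = 0.05 two-sided and β = 0.2.

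- Normal approximation: n = 2(1.960 + 0.842)² / 1.2² = 15.70 / 1.44 = 10.9, so 11 per group.
- Noncentral t: 12 per group gives power 0.802; 13 per group gives 0.835.

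The stated 13 is therefore reproduced to within 2 patients on this reading. A repeated-measures version depends on a correlation that the article does not give: for f = 0.6 it needs 7 to 12 per group as the correlation runs from 0 to 1. The blinding point does not depend on this figure.

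**3. What a reading shift would do.** Inputs: n = 13 per arm (Sample size), threshold 0.05 (Statistical analysis, read as two-sided), true difference 0, and an assumed systematic shift of b SD of the change score between arms. The documents give no value for b. With two time points, the group-by-time test is equivalent to a two-sample t test on change scores with 2 × 13 − 2 = 24 degrees of freedom. The noncentrality is

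δ = b × √(n/2) = b × √6.5 = 2.550 b.

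The false-positive rate is P(|T| > t₀.₉₇₅,₂₄), with T noncentral t with parameter δ.

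| Assumed shift b (SD) | δ | False-positive rate, one outcome |
|---|---|---|
| 0 | 0 | 5.0% |
| 0.1 | 0.255 | 5.7% |
| 0.25 | 0.637 | 9.4% |
| 0.5 | 1.275 | 23.2% |

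**4. The other direction.** A shift can also hide an effect. If the true difference were 1.2 SD and the reader's shift were 0.2 SD against it, the apparent difference would be 1.2 − 0.2 = 1.0 SD. Power at 13 per arm would then fall from 83.5% to 68.7%. The 0.2 SD is again only an assumption.

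**5. Reader reliability, a separate point.** The Intervention section has one person measuring everything twice. The Statistical analysis section plans an ICC between two examiners. Duplicate readings by one person yield an intra-examiner ICC; a between-examiner ICC needs a second reader, whom the measurement procedure does not mention.

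**The case against.** **Visibility is inferred.** A reader of the protocol might conclude that the assessor cannot be blind and learns the arm from every follow-up film. The documents do not support that. No sentence says how clearly the ANS area shows on these films, and there are plates on the maxilla in both arms. That the spine's absence is likely to be noticed follows from the surgery and imaging described; how often is undocumented. This objection stands, and it limits the claim to many or most films.

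**Masking may be described elsewhere.** A journal article condenses the full protocol, so film handling could be specified there. Silence about cropping would not be a finding by itself. However, the article makes a positive claim of concealment and then describes a procedure that, as written, does not provide it. The objection softens the point to blinding not secured; it does not remove it.

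**The sizes are generic.** The shifts in the table come from no passage, and the same rates would apply to any systematic bias in a trial of this size. It would be wrong to infer that this trial's error rate is 9% or 23%. The stated hypothesis is one of no difference, and surgeons are described as divided, so no motive to favour an arm is evident. Baseline readings made before surgery cannot be influenced by the arm. All of this stands: size and direction are unknown.

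**The ICC conflict is a different matter and may be explicable.** The same-person wording could mean only that each patient's two films share a reader. Training and calibration mentions two team members trained in accuracy and reproducibility, so a two-examiner calibration exercise is possible. The passages need reconciling; an impossible analysis is not shown, and this adds nothing to the blinding point.

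**Masking may be incomplete.** Challenges and limitations notes that excessive ANS removal may leave a depression below the nose. That soft-tissue cue would survive covering the bone, so full masking should not be promised.

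**Conclusion.** The point holds in limited form. The article claims a concealed assessor, but the procedure it describes is likely to reveal the arm on many or most follow-up films. Assessor blinding is therefore not secured as written, and both stated outcomes are open to detection bias.

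This rests on one inference, that complete removal of the ANS is usually recognisable on a lateral cephalogram to a trained reader who has also read the baseline film. The figures of 5.7%, 9.4% and 23% are conditional on assumed shifts of 0.1, 0.25 and 0.5 SD with no true effect and 13 per arm. They show how sensitive a trial of this size is to a reading shift, not how large the shift will be. Bias towards no difference is as possible as bias away from it.

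**What to change.** 1. **Mask the films before reading.** Someone other than the reader covers the bony ANS zone on all 52 films (26 patients × 2), in the same way in both arms and at both time points. Check first that the landmarks for nasolabial angle and upper lip length remain readable. Both outcomes are soft-tissue measures, so this should be possible, but the documents do not establish it.
2. **Code and shuffle.** The same person codes the films and passes them in random order to the single reader, who should not have been in theatre.
3. **Restate the Blinding section**, for example: *allocation code withheld and ANS region masked; residual soft-tissue cues possible*. If masking proves infeasible, drop the claim of a blinded assessor and report this as a limitation.
4. **Separately, reconcile the reliability plan.** Either name the second examiner and what that person reads, or replace the two-examiner ICC with an intra-examiner ICC and within-subject SD from the duplicate readings already planned.

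Cost: image-preparation time, a re-read of the baseline films within the shuffled set, and a few sentences of text. No new visits, exposures or readers are needed. The remaining drawback is that masking may be imperfect, which the reworded statement acknowledges.
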